### Power analysis

A power analysis was performed using G*Power (version 3.1.9.4). Because capillary-fiber perimeter exchange index (CFPE) is a widely measured variable and an important component of anticipated adaptations, we used the results from Kim et al.[27] to power this study. They observed significantly greater CFPE with LHT vs CON (d > 1.5). We used a more conservative, d = 1.2 (reduced by 20%), because older adults might have a blunted response to LHT. We used the statistical analysis of Aim 1 to power the study because it involves more groups (three) and thus requires the largest number of participants. The one-way ANOVA with three groups (d = 1.2, f = 0.4899, α = 0.05) will require 45 total participants (15 per group) to achieve 80% power. This will be followed by two non-orthogonal planned contrasts (CON vs. LHT, LHT vs. HIIT). These *t*-*t*ests (d = 1.2, α = 0.05/2 [Bonferroni]) also require 15 participants per group to achieve 80% power. In the statistical analysis of Aim 2, only two of the three groups are included, leading to greater statistical power. The planned *t*-*t*est (d = 1.2, a = 0.05, 15 participants per group) will achieve 89% power. If needed, the one-way ANOVA with two groups (d = 1.2, a = 0.05, 15 participants per group) will also achieve 89% power. Comparing this number of participants per group to previously published work examining LHT and SKM mitochondria, capillarization, and size [26–28], 15 participants per group is a comparable estimate of sample size. Although not identical to our proposed work, sample sizes of 10 (within-subjects) [23] and 18 (9 per group, between-subjects) [31] were sufficient to detect improvements in glycemic control in overweight men and in obese women with polycystic ovarian syndrome, respectively, in response to whole-body heat therapy. Our power analysis and previously published research support a target sample size of 15 participants per group (CON, HIIT, and LHT). Accounting for a potential 18% attrition rate, we aim to enroll 18 participants per group (9 men, 9 women) for a total target enrollment of 54 participants.

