#### Randomization and stratification.

Participants are stratified based on sex assigned at birth (male, female), age brackets (e.g., 50–59, 60–69 years, 70–79, etc.), and glucose tolerance (glucose concentration at the 1-hour blood draw following ingestion of 75 g glucose: < 155 mg/dL, normal glucose tolerance; 155 to <209 mg/dL, intermediate hyperglycemia; and ≥209, potential T2D) [37] at baseline. A permuted block randomization method [38] with a block size of three (1:1:1 ratio) is used within each stratum to ensure balanced allocation among groups (CON, HIIT, LHT). Accordingly, an allocation table is used to randomize participants to groups. Group assignments are recorded in a separate randomization form, accessible only to a designated unblinded investigator, on the HIPAA-compliant Research Electronic Data Capture (REDCap)2 database, adhering to NIH guidelines for clinical trials. This balanced permuted block randomization can ensure baseline comparability between treatment groups, allow further analysis of treatment effects for different subgroups, and maximize statistical power.

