### Statistical analyses

All outcome measures at T1, T2, and T3 will be summarized using descriptive statistics. The study evaluates treatment efficacy by analyzing changes across three distinct time points (T1, T2, and T3). While the data are longitudinal, the primary aims focus on the magnitude of change within specific intervals. Therefore, the magnitude of change between time points for each outcome measure will be calculated for analyses.

To achieve Aim 1 (comparing LHT with CON and LHT with HIIT; k = 3), changes between T1 and T2 values (i.e., before and after Phase 1) for all muscle architecture outcomes, glycemic control outcomes, and frailty risk indicators will be calculated and checked for the assumption of normality using the Shapiro-Wilk test. An appropriate transformation will be conducted if normality is violated. Then, one-way ANOVA with three groups (CON, HIIT, LHT) will be run. This will be followed by two non-orthogonal planned contrasts (CON vs. LHT, LHT vs. HIIT). The Bonferroni correction will be used to control the familywise error rate.

To achieve Aim 2 (comparing LHT with CON after participants in both groups undergo HIIT during Phase 2 of the study; k = 2), changes between T2 and T3 values for all muscle architecture outcomes, glucose tolerance outcomes, and frailty risk indicators will be calculated and checked for the assumption of normality using the Shapiro-Wilk test. An appropriate transformation will be conducted if normality is violated. Then, a *t* test will be run to compare CON and LHT, and confidence intervals will be constructed to compare each variable between the two treatment groups. If improvements for participants in the LHT group from T1 to T2 make the absolute change from T2 to T3 smaller, we will also compare the combined improvements across both phases for the 2 treatment groups. Changes between T1 and T3 in muscle architecture outcomes, glucose tolerance outcomes, and frailty risk indicators will be calculated and transformed if needed. ANOVA analyses will be run and confidence intervals constructed to compare the combined improvements of each factor between the two treatment groups (CON and LHT). We can also employ a one-way ANCOVA for the T2-to-T3 analysis, including the T1-to-T2 change score as a covariate. This ANCOVA method can clarify the relationship between early-phase response and late-phase progress.

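### Aim 1 tests its two planned contrasts by plain Bonferroni, which is valid; Holm's step-down would give the same 5% familywise control with power never lower (a cheap improvement, not an error)

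*Protocol article*

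**What the plan says.** The Statistical analyses section runs a one-way ANOVA on the T1-to-T2 changes in the three groups and then states: "This will be followed by two non-orthogonal planned contrasts (CON vs. LHT, LHT vs. HIIT". For multiplicity it adds: "The Bonferroni correction will be used to control the familywise error rate". It does not make the contrasts depend on a significant F test.

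The Power analysis section uses the same rule. For the contrast tests it gives "d = 1.2, α = 0.05/2 [Bonferroni]) also require 15 participants per group to achieve 80% power". For the omnibus test it gives "d = 1.2, f = 0.4899, α = 0.05) will require 45 total participants (15 per group) to achieve 80% power". The effect size is traced to an earlier study of LHT against control: "We used a more conservative, d = 1.2 (reduced by 20%), because older adults might have a blunted response to LHT".

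**The concern.** Plain Bonferroni tests each contrast at 0.025 whatever the other one shows. Holm compares the smaller p-value with 0.025 and, if that rejects, compares the larger with 0.05. Both hold the familywise error at 5% without any assumption about the correlation between the contrasts, which share the LHT arm. For testing alone, Bonferroni therefore has no advantage.

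What is at stake is the second answer in Aim 1. A contrast with a p-value between 0.025 and 0.05 is not declared significant under the plan even when the other contrast is clearly significant. With about 15 completers per group this can matter, chiefly for LHT vs HIIT if that difference is the smaller one.

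**Working it through.** **Inputs.** From Power analysis: d = 1.2, 0.025 per contrast, f = 0.4899, 15 per group. From Randomization and stratification: 1:1:1 allocation. Tests are taken as two-sided. The document does not say so, but the stated 89% for Aim 2 reproduces on that basis (88.7%).

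**Step 1: the plan's own figures.**
- Contrast: noncentrality = d × √(n/2) = 1.2 × √7.5 = 3.29, with 28 df and two-sided 0.025. Power is 81.5% at n = 15 and 78.2% at n = 14, so 15 is the smallest number that reaches 80%.
- Omnibus: noncentrality = f² × N = 0.24 × 45 = 10.8, with 2 and 42 df. Power is 81.7%.
- Contrast on the pooled ANOVA error (42 df): 82.8%.

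The stated figures reproduce.

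**Step 2: error control under Holm.**
- If both nulls are true, a false rejection needs the smaller p-value to be at or below 0.025, which has probability at most 2 × 0.025 = 0.05.
- If one null is true, a false rejection needs that p-value to be at or below 0.05, again with probability at most 0.05.
- Simulated familywise error with all means equal is 4.6% for both methods. With LHT = HIIT and CON lower, the false rejection rate for LHT vs HIIT is 2.5% under Bonferroni and 4.4% under Holm, both within 5%.

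**Step 3: which means fit the stated f.** With SD 1, f = √(Σ(mean − grand mean)²/3).
- CON 0, HIIT 0.6, LHT 1.2: √((0.36 + 0 + 0.36)/3) = 0.4899. This matches.
- CON 0, LHT 1.2, HIIT 0: √((0.16 + 0.64 + 0.16)/3) = 0.566.
- CON 0, LHT 1.2, HIIT 2.4: √((1.44 + 0 + 1.44)/3) = 0.980.

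The document gives no group means, so every pattern is an assumption.

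**Step 4: power, Bonferroni → Holm.** Simulation of 200,000 trials per pattern, 15 per group, pooled error with 42 df. The simulation error is about 0.1 point, since √(0.25/200,000) = 0.0011. Both methods were applied to the same simulated trials.

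| Means (CON, LHT, HIIT) | CON vs LHT | LHT vs HIIT | At least one |
|---|---|---|---|
| 0, 1.2, 0.6 (f = 0.4899) | 82.8% → 83.3% | 25.9% → 35.4% | 83.7%, unchanged |
| 0, 1.2, 0 | 82.9% → 87.2% | 82.7% → 87.2% | 92.7%, unchanged |
| 0, 1.2, 2.4 | 82.7% → 88.9% | 82.9% → 89.1% | 99.2%, unchanged |
| 0, 1.2, 1.2 (only CON vs LHT real) | 82.7% → 82.9% | no true difference | 83.4%, unchanged |

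In the last row the gain for CON vs LHT is 0.1 to 0.2 points (82.74% → 82.87%). Ordinary two-sample t tests (28 df) give the same picture: 25.1% → 34.5% for LHT vs HIIT in the first row, and 81.4% → 81.6% for CON vs LHT in the last.

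The last column cannot change: both methods make their first rejection by the same rule, smaller p-value against 0.025.

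**The case against.** The strongest reply is that nothing here is wrong. Bonferroni is valid, prespecified, and consistent between the Power analysis and Statistical analyses sections. It also yields simultaneous intervals that always agree with its tests, which Holm does not simply provide. All of this stands, and it is why the point is an improvement and not a correction.

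Three stronger readings are tempting, and the document does not support them.

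- *That Bonferroni erodes the planned 80%.* It does not. The 80% was computed at 0.025, so the correction is already paid for, and Holm's gain comes on top.
- *That the trial is short of power to show both contrasts.* If both are d = 1.2, the chance that both reject does rise, from 73% to 82% (LHT above both arms) or from 66% to 79% (LHT between them). But the document never makes joint rejection a criterion of success, and it sizes each contrast separately. These patterns also give f = 0.566 or 0.980, not 0.4899. One has HIIT no better than sham, against the Introduction's account of HIIT; the other has HIIT 2.4 SD above sham, a figure that appears nowhere.
- *That the plan is conservative twice because the ANOVA is a gate.* The text only says that the contrasts follow the ANOVA. If it were a gate, familywise error under equal means would be 3.6%. But even unadjusted contrasts would then hold it (4.2% under equal means, and about 5% for the true null when the other contrast is real), so Holm would not be the sharpest remedy either.

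The reply does not give Bonferroni any advantage in testing. Preferring tests and intervals that always agree is a legitimate reason to keep it, but the document does not give that reason.

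**Conclusion.** The point holds as a low-cost improvement. The plan's method is valid and delivers its stated power. Holm keeps the same 5% familywise error and never rejects less.

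The size of the gain depends on means that the document does not state. Under the assumed spacing that fits f = 0.4899 it is about 9 to 10 points for LHT vs HIIT, which still leaves that contrast at only about 35%, and LHT vs CON is essentially unchanged at 83%. It is about 4 to 6 points per contrast if both are truly d = 1.2, and at most about 0.2 points if only LHT vs CON is real. It is nil for the chance of at least one rejection. These figures assume 15 completers per group, normal outcomes with equal variances, and two-sided tests.

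**What to change.** In Statistical analyses, Aim 1, replace the Bonferroni sentence with one to this effect: *The two planned contrasts will be tested with Holm's step-down procedure at a familywise level of 0.05 per outcome, whatever the result of the omnibus F test; confidence intervals for the contrasts will be Bonferroni-adjusted.* This also settles that the ANOVA is not a gate.

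The sample size and the stated 80% stay as they are. The smaller p-value is still tested at 0.025, so the present calculation becomes a lower bound for the power of each contrast under the same assumptions.

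The cost is one sentence, with no added participants, visits or data, plus the IRB review that the Study overview requires for any protocol change. It should be made before comparative results are seen, and the Data management section plans interim analyses every 6 months from the second year. The one downside is that a Bonferroni-adjusted interval may occasionally include zero where Holm rejects; a line in the report saying so is enough.

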The magnitude of angiogenic adaptations to local heat therapy (LHT) can be similar to whole-body heating [29], providing a foundation to support examination of the therapeutic potential of LHT. Although it has not been examined in individuals with prediabetes, a single lower body exposure to hot water circulation at 43°C for 90 min in patients with peripheral artery disease tended to improve walking performance [30]. Given these promising initial findings, LHT may be useful to improve muscle architecture (i.e., capillarization, mitochondria, muscle fiber CSA). Such changes could improve exercise tolerance by preconditioning the microenvironment of SKM, likely enhancing exercise adherence and improving subsequent exercise adaptations. Therefore, changes in the SKM with LHT alone, and with exercise training following LHT, may improve glycemic control and physical function, thereby decreasing risk for T2D and frailty, in older individuals.

Strong evidence supports the benefits of heat therapy on SKM and glycemic control. However, the efficacy of LHT to decrease risk for T2D and frailty in older adults with prediabetes has not been examined. Therefore, we developed the Heat and Exercise in Aging as Therapy (HEAT) study. This randomized, controlled clinical trial aims to evaluate the effectiveness of LHT among older adults with prediabetes using a two-phased approach. The aim of Phase 1 is to compare the effectiveness of LHT alone versus HIIT to improve muscle architecture, glycemic control, exercise capacity, and risk of frailty (Aim 1). The aim of Phase 2 is to assess whether a period of LHT preceding the initiation of HIIT improves exercise responsiveness, resulting in further improvements in SKM architecture, glycemic control, and risk of frailty (Aim 2). Given the practicality and ease of LHT application, findings can be easily translated to clinical recommendations.

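### The Aim 2 T1-to-T3 comparison adds the Phase 1 heat effect back in, so it tells nothing about exercise responsiveness beyond T2-to-T3, and the plan does not limit how it may be read

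*Protocol article*

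**What the plan says.** The Introduction states the Aim 2 question: to "assess whether a period of LHT preceding the initiation of HIIT improves exercise responsiveness", with further gains in muscle architecture, glycaemic control and frailty risk expected to follow.

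The Statistical analyses section gives the Aim 2 analysis in this order:

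- **Main comparison.** "changes between T2 and T3 values for all muscle architecture outcomes, glucose tolerance outcomes, and frailty risk indicators will be calculated", and CON and LHT are compared by a t test with confidence intervals.
- **Trigger.** A further comparison follows under this condition: "If improvements for participants in the LHT group from T1 to T2 make the absolute change from T2 to T3 smaller". No numerical rule is given.
- **Added comparison.** In that case "we will also compare the combined improvements across both phases for the 2 treatment groups", using T1-to-T3 change, ANOVA and confidence intervals.
- **Optional ANCOVA.** T2-to-T3 change may also be analysed with the T1-to-T2 change as covariate.

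The T1-to-T2 difference between CON and LHT is already one of the two planned contrasts of Aim 1. The section does not say that the T1-to-T3 result answers a different question from the T2-to-T3 result.

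**The concern.** Aim 2 is a question about what happens during Phase 2. A T1-to-T3 contrast also contains everything that happened in Phase 1. If heat alone works and the gain is kept, the LHT group is ahead at T3 even when it responds to HIIT exactly as the sham group does.

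The trigger adds to the difficulty. The cumulative contrast is called for when the LHT group's T2-to-T3 change is smaller, a pattern that does not show better responsiveness. A significant T1-to-T3 result reported under Aim 2 could then be taken as support for preconditioning when it shows only that heat worked in Phase 1 and the gain lasted. Preconditioning is the distinctive claim of Phase 2, so what may count as evidence for it should be settled in the plan.

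**Working it through.** **Inputs from the Power analysis section:** 15 completers per group, alpha 0.05, d = 1.2, and 89% power for the Aim 2 t test and for the two-group ANOVA to be used if needed. The d is a reduced value from a study of heat alone: "They observed significantly greater CFPE with LHT vs CON (d > 1.5"). It is a heat effect on the capillary-fiber perimeter exchange index (CFPE), not a preconditioning effect.

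**Assumptions not in the document:** two-sided tests; the trigger read as LHT mean T2-to-T3 change below CON's; the ratio of the T1-to-T3 change SD to the T1-to-T2 change SD taken as 1 (equal visit variances and correlations) or 1.41 (independent increments); net T2-to-T3 differences of 0, -0.3 and -0.6 SD. Effects are in SDs of the T1-to-T2 change.

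**Step 1: the plan's figure.** Noncentral t with d = 1.2, n = 15 per group and two-sided 0.05 gives power 0.887. The two-group ANOVA with f = 0.6 and N = 30 also gives 0.887. The stated 89% is reproduced.

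**Step 2: identity.** For each participant, (T3 - T1) = (T2 - T1) + (T3 - T2). Taking group means,

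LHT-CON difference in T1-to-T3 = LHT-CON difference in T1-to-T2 + LHT-CON difference in T2-to-T3.

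The first term is the Aim 1 contrast. Only the second bears on the response to HIIT.

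**Step 3: T1-to-T3 test before any trigger.** Standardised effect = (1.2 + net T2-to-T3 difference) / SD ratio.

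| Net T2-to-T3 difference | Effect, ratio 1 | Power | Effect, ratio 1.41 | Power |
|---|---|---|---|---|
| 0 | 1.2 | 0.887 | 0.851 | 0.614 |
| -0.3 | 0.9 | 0.663 | 0.638 | 0.393 |
| -0.6 | 0.6 | 0.355 | 0.426 | 0.203 |

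A net difference of -0.3 is the same as keeping 75% of the Phase 1 gain (1.2 × 0.75 = 0.9), and -0.6 the same as keeping half (1.2 × 0.5 = 0.6). A weaker response to HIIT and fading of the heat gain are therefore one scenario here, not two.

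**Step 4: with the trigger (simulation).** P(either) = P(trigger) × P(T1-to-T3 favours LHT given trigger) + P(T2-to-T3 favours LHT). The two events cannot occur together, because a significant T2-to-T3 result for LHT means that the trigger has not fired.

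| SD ratio | Net T2-to-T3 difference | P(trigger) | T1-to-T3 favours LHT, given trigger | T2-to-T3 favours LHT | Either |
|---|---|---|---|---|---|
| 1 | 0 | 0.50 | 0.81 | 0.025 | 0.43 |
| 1 | -0.3 | 0.79 | 0.61 | 0.003 | 0.48 |
| 1 | -0.6 | 0.95 | 0.33 | <0.001 | 0.32 |
| 1.41 | 0 | 0.50 | 0.38 | 0.025 | 0.22 |
| 1.41 | -0.3 | 0.79 | 0.29 | 0.003 | 0.23 |
| 1.41 | -0.6 | 0.95 | 0.17 | <0.001 | 0.16 |

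First row: 0.50 × 0.81 + 0.025 = 0.43.

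**Step 5: source of the excess.** With no Phase 1 effect and no T2-to-T3 difference, P(either) at SD ratio 1 is about 2.7%. The excess comes from the carried-over heat gain, not from having two tests.

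**The case against.** The strongest reply is that the plan does nothing improper. It describes the contrast openly as spanning both phases, adds it to the T2-to-T3 test rather than replacing that test, and never says that a T1-to-T3 advantage will be called preconditioning. The comparison is randomised and referenced to baseline. It fits the study overview's broader interest in LHT applied before HIIT. All of this stands. A reader might infer that the investigators intend to claim preconditioning from T1-to-T3; the document does not support that inference.

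The trigger also has a sensible motive. A smaller absolute gain from a better T2 value may reflect a ceiling, or fading of the heat gain. So the stronger reading, that a smaller T2-to-T3 change shows heat to have blunted the response to HIIT, does not follow either. The pattern is ambiguous; it simply does not show better responsiveness.

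On size, the untriggered 89% should not be taken as the error rate of the Aim 2 procedure, since it ignores the trigger. The significant T1-to-T3 results counted above are correct findings about the whole sequence. They mislead only if used to answer the responsiveness question. And d = 1.2 is given for CFPE, so the percentages do not carry over to glycaemic or frailty outcomes.

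What remains is that the article itself fixes the contrast, its trigger and its place under Aim 2, and leaves open what a favourable result may support. The optional ANCOVA does not settle this: it conditions on a post-randomisation change that shares the T2 measurement with the outcome.

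**Conclusion.** The concern holds as a matter of interpretation that the plan leaves open. The T1-to-T3 comparison is valid for the total effect of LHT then HIIT against sham then HIIT, but says nothing about exercise responsiveness that T2-to-T3 does not already say. If either result were accepted for Aim 2, the chance of a significant LHT advantage with no net T2-to-T3 difference would be about 43% with equal change SDs, or about 22% with the larger T1-to-T3 SD, against 2.5% for T2-to-T3 alone. With net differences of -0.3 and -0.6 SD it would be about 48% and 32% (23% and 16% with the larger SD). These figures depend on the assumed Phase 1 effect, the SD ratio and the numerical form given to the trigger. The identity behind them depends on none of these. The change should be made, because it decides what the trial can conclude about preconditioning.

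**What to change.** In the Aim 2 paragraph of the Statistical analyses section:

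1. Base the conclusion on exercise responsiveness only on the LHT-CON difference in T2-to-T3 change.
2. Report the T1-to-T3 comparison for every outcome, without the trigger, and name it the total effect of the sequence.
3. Show it beside the T1-to-T2 and T2-to-T3 differences that add up to it.
4. State that a T1-to-T3 advantage alone is not evidence of preconditioning.

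The cost is a few sentences; no new data or participants are needed. The small downside is that a favourable T1-to-T3 result can no longer support the preconditioning claim.

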Because the study utilizes balanced permuted block randomization, we expect key baseline characteristics, such as sex assigned at birth, age, and glucose tolerance, to be well-balanced across the three treatment groups. Our analysis will begin with a one-way ANOVA to evaluate primary treatment effects. To ensure the model is both parsimonious and robust, we will perform residual diagnostics by plotting residuals against various participant characteristics (demographic, clinical, and molecular). Non-random residual distributions will signal the need to include missing main effects, while diverging patterns across treatment levels will indicate potential interaction effects. These additional terms will be formally tested for significance before being integrated into the final model.

Note that integrating covariates into the model generally enhances the power to detect treatment effects by reducing error variance. Conversely, the power to detect interaction effects is usually low, as these effects typically exhibit smaller magnitudes and larger standard errors. Given that our sample size is determined based on a one-way ANOVA, all interaction analyses will be treated as exploratory.

While we anticipate complete data sets for primary outcomes assessed at T1, T2, and T3, there is a possibility of missing data. To address potential bias and maintain statistical power in the presence of potential missing data, we will employ Multiple Imputation by Chained Equations. We will generate several imputed datasets using all available baseline characteristics and previous timepoint values. Each dataset will be analyzed independently using the specified ANOVA or ANCOVA model, and the resulting estimates and standard errors will be pooled to produce a single inference according to Rubin’s Rules. This approach accounts for both within-imputation and between-imputation uncertainty.

To assess the robustness of our primary findings, a sensitivity analysis will be performed. While the primary analysis assumes data are Missing At Random, we will explore the impact of Missing Not At Random data. Specifically, we will apply a penalty to the imputed values of the treatment group to simulate a scenario where participants who dropped out had poorer outcomes than those who remained. If the treatment effect remains statistically significant under these conservative assumptions, the primary results will be considered robust.

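### Aim 2 adds an undefined data-dependent T1-to-T3 comparison and an ANCOVA on a post-randomisation change score, neither of which estimates the preconditioning effect

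*Protocol article*

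**What the plan says.** The Introduction sets Aim 2 as a question about the response to training: to "assess whether a period of LHT preceding the initiation of HIIT improves exercise responsiveness".

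The Statistical analyses section then describes three LHT-CON analyses.

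- **Default.** The t test on the T2-to-T3 change is described so: "test will be run to compare CON and LHT, and confidence intervals will be constructed to compare each variable between the two treatment groups". No condition is attached. The Power analysis section calls this test planned and gives it 89% power.
- **Conditional addition.** The T1-to-T3 changes come in under a condition: "If improvements for participants in the LHT group from T1 to T2 make the absolute change from T2 to T3 smaller, we will also compare". For these, "ANOVA analyses will be run and confidence intervals constructed to compare the combined improvements of each factor between the two treatment groups (CON and LHT"). Smaller than what, by how much, and outcome by outcome or overall, is not stated.
- **Optional model.** "We can also employ a one-way ANCOVA for the T2-to-T3 analysis, including the T1-to-T2 change score as a covariate". The reason given is: "This ANCOVA method can clarify the relationship between early-phase response and late-phase progress".

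Only interaction analyses are called exploratory. The missing-data paragraph says of the imputed data: "Each dataset will be analyzed independently using the specified ANOVA or ANCOVA model". Bonferroni is named for Aim 1; no order or error control is stated among the three Aim 2 analyses.

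**The concern.** The T1-to-T2 change is not a baseline variable. Randomisation follows T1 testing (Blinding and unblinding), so in the LHT and CON arms this change is the Phase 1 response itself. The Power analysis section assumes that LHT shifts it by d = 1.2 relative to CON. Adjusting for it compares LHT and CON participants who happened to have the same Phase 1 response, which is no longer the randomised comparison.

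There is also an arithmetic link. The T2 value enters the covariate (T2 minus T1) with a plus sign and the outcome (T3 minus T2) with a minus sign. A T2 reading that is high by chance raises one and lowers the other, which pushes the within-arm slope below zero. For muscle outcomes such noise is plausible, because the Muscle biopsy section takes each visit's sample from a different site, 3 cm from the midpoint used at T1.

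The T1-to-T3 change is the sum of the Phase 1 and Phase 2 changes. A treatment that works in Phase 1 and does nothing for the later response to HIIT can still give a significant T1-to-T3 difference. At stake is the Aim 2 conclusion: a Phase 1 effect could be reported as preconditioning, or real preconditioning could be adjusted away.

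**Working it through.** **Inputs.** From the Power analysis section: 15 per group, alpha 0.05 (two-sided assumed, since sidedness is not stated), d = 1.2. From the Statistical analyses section: the three analyses above. Not in the document and therefore assumed: rho, the within-arm correlation of the T1-to-T2 and T2-to-T3 changes, over the range -0.5 to +0.25. Each change score is given an SD of 1.

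**The plan's own figure.** Two-sample t test with 28 df and noncentrality 1.2 x sqrt(15/2) = 3.29: power 0.887. The two-group ANOVA with f = 0.6 and N = 30 also gives 0.887. The stated 89% reproduces.

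**Bias of the ANCOVA.** Let d1 be the LHT-CON difference in the T1-to-T2 change and d2 that in the T2-to-T3 change. With equal SDs the within-arm slope is rho, so the adjusted arm difference is d2 - rho x d1. With no Phase 2 difference (d2 = 0) this equals -rho x d1.

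**Why rho = -0.5 is a natural reference.** Suppose visit errors e1, e2, e3 are independent with equal variance s² and all participants in an arm respond alike. Then cov(e3 - e2, e2 - e1) = -s² and var(e2 - e1) = 2s², so the slope is -1/2. The adjusted difference is 0 - (-0.5)(1.2) = +0.60 SD although preconditioning is zero.

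**Simulation.** 40,000 trials per row, 15 per arm, d1 = 1.2, d2 = 0. The trigger is read as LHT's mean change being larger than CON's in Phase 1 and smaller in Phase 2; it then fires in 50% of trials.

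| rho | ANCOVA bias (SD) | ANCOVA significant | of which for LHT | T2-to-T3 t test significant | t test or triggered T1-to-T3 significant |
|---|---|---|---|---|---|
| -0.5 | +0.60 | 33.5% | 33.5% | 5.0% | 44% |
| -0.4 | +0.48 | 21% | 21% | 5.1% | 40% |
| -0.25 | +0.30 | 11% | 10.6% | 5.3% | 34% |
| -0.1 | +0.12 | 5.6% | 4.4% | 4.8% | 27% |
| 0 | 0.00 | 4.9% | 2.4% | 4.9% | 24% |
| +0.25 | -0.30 | 11% | 0.4% | 5.0% | 17% |

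The nominal rate for significance in favour of LHT is 2.5%. With a smaller Phase 1 effect, d1 = 0.6, and rho = -0.5, the bias is 0.5 x 0.6 = +0.30 SD and 14% of trials are significant.

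**Masking.** If a true +0.6 SD preconditioning effect acts wholly through the Phase 1 change (rho = +0.5, beyond the range above), the ANCOVA estimates 0.00 and rejects in 5% of trials. The plain t test rejects in 35%.

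**Why the last column is high.** The T1-to-T3 difference is d1 + d2 = 1.2 with SD sqrt(2 + 2 x rho). Its standardised size is 1.2/1 = 1.2 at rho = -0.5 and 1.2/1.41 = 0.85 at rho = 0. Run alone it is significant in 88% and 61% of trials. These are correct detections of the total effect, but they say nothing about preconditioning.

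**No LHT effect in either phase.** The t test plus the triggered T1-to-T3 test rejects in 4.9% to 5.3% of trials under the reading above. It rejects in about 7% if the trigger is read without the Phase 1 condition. The text does not settle which reading applies.

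**The case against.** The strongest reply is that the default test is sound. The T2-to-T3 t test is unconditional, powered, and holds 5% in every row of the table. The ANCOVA is optional and its stated purpose is to relate early to late response, which is a legitimate descriptive question. The reference to an ANCOVA in the missing-data paragraph may mean the covariate-adjusted models described in the same part of the section. Order and labels are often left to a statistical analysis plan, and none is shown. All of this stands and limits the severity. It does not remove the point: the article itself chooses the post-randomisation covariate, attaches it to the T2-to-T3 analysis that compares the arms, and sets a results-based condition for T1-to-T3.

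Four stronger readings may tempt a reader, and the document does not support them.

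- That Aim 2 picks its contrast after seeing the data. T1-to-T3 is added to the t test, not put in its place.
- That the ANCOVA must produce a false benefit. This needs a negative rho. There is no bias at zero and the sign reverses at positive rho, and the document gives no value. The -0.5 case rests on identical responses and independent, equal visit error.
- That the trigger seriously inflates the error rate when LHT does nothing. This depends on the reading, from about 5% to about 7%.
- That a significant T2-to-T3 result against LHT, when both arms reach the same T3 level, is a false positive. It occurs in 89% of trials at d = 1.2, but LHT's Phase 2 gain is then truly smaller. It is a hazard of interpretation, and the T1-to-T3 comparison was evidently meant to address it.

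**Conclusion.** The concern holds in limited form. The change-score ANCOVA does not estimate the Aim 2 effect. At d1 = 1.2 its bias runs from +0.60 SD (about 34% of trials significant for LHT) at rho = -0.5, through nil at rho = 0, to -0.30 SD at rho = +0.25. Size and direction therefore rest on a correlation that the protocol does not give, and on the planning effect, which was derived for one capillarization index, applying to the outcome in question. The triggered T1-to-T3 comparison has no defined rule and carries the Phase 1 effect. With that effect and no Phase 2 difference, it or the t test is significant in about 24% (rho = 0) to 44% (rho = -0.5) of trials under the trigger reading used here. The main Aim 2 test is valid; the fault lies in what is placed beside it without an order or a label.

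**What to change.** In the Aim 2 paragraph of the Statistical analyses section:

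1. Name the unadjusted LHT-CON difference in the T2-to-T3 change as the primary Aim 2 test. It holds 5% and keeps the planned 89% power at d = 1.2.
2. Delete the condition on T1-to-T3. Always report that difference as a secondary total-effect contrast, and state that it is not by itself evidence of preconditioning. Adjustment for the T1 value and the stratification factors is acceptable here. It should not become the primary test: in simulation with d1 = 1.2, a persisting Phase 1 effect and zero preconditioning, T3 adjusted for T1 was significant in 91% to 97% of trials.
3. Drop the ANCOVA on the T1-to-T2 change as a comparison of arms. If the early/late relation is of interest, report the association within each arm, labelled descriptive.
4. State that a smaller T2-to-T3 gain in LHT may reflect a higher T2 level and is to be read together with T1-to-T3.

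The cost is wording only, with no new data or visits. The one loss is an optional model. Data collection is planned to run to February 2029, so the change can be made before the final data are seen.
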